## Abstract

**Introduction:**

Subclinical hypothyroidism (SCH) is a common endocrine disorder characterized by elevated thyroid-stimulating hormone (TSH) levels and normal free thyroxine (FT_4_) levels. The overdiagnosis and overtreatment of SCH in elderly patients have become concerns as TSH levels naturally increase with age. Studies have shown that many elderly patients with SCH can recover without treatment, and the administration of levothyroxine (L-T_4_) does not improve their prognosis. Therefore, It is necessary to establish age-specific reference ranges for TSH in elderly individuals to aid in clinical decision-making and prevent overdiagnosis.

**Methods:**

This is a multicenter prospective study that focuses on Chinese elderly patients with SCH who have TSH levels below 10 mU/L. After obtaining the informed consent of the patients, their initial diagnosis information will be registered, and they will be asked to fill out questionnaires such as the Montreal Cognitive Assessment-Basic (MoCA-B), Hamilton Depression Scale (HAMD), Hypothyroidism Symptom Questionnaire (SRQ), frail scale(FRAIL), fatigue scale, and EQ-5D. In addition, thyroid function tests, blood lipid analysis, carotid artery ultrasound, and thyroid ultrasound examinations will be conducted. Patients will also be grouped according to FT_4_ levels, the changes in FT_4_ and its relationship with TSH can also be described. For patients over 80 years old, a decrease in FT_4_ will be used as an endpoint event, while for patients between 60-80 years old, TSH levels greater than or equal to 10mIU/L or a decline in FT_4_ will be used as the endpoint event. The TSH reference intervals of the general and elderly populations will be used to calculate medical costs associated with multiple follow-ups of patients, and a social-economic analysis will also be conducted.

**Discussion:**

This study will prospectively observe elderly patients with SCH who are screened using both age-specific and non-age-specific TSH reference ranges for the elderly population. We will compare the results of elderly patients diagnosed with SCH using different reference ranges and analyze their association with FT_4_ to identify meaningful SCH patients and reduce over diagnosis and over treatment of elderly SCH.

**Ethics:**

The Medical Science Research Ethics Committee of the First Affiliated Hospital of China Medical University approved this study (ID: AF-SOP-07-1.1-01). The results will be published in an open-access journal.

**Clinical trial registration:**

https://www.chictr.org.cn/, identifier ChiCTR2300070831.

## Introduction

Subclinical hypothyroidism (SCH) is characterized by elevated serum thyroid-stimulating hormone (TSH) and normal thyroid hormone levels (1). As TSH is considered a good indicator of thyroid function, the diagnosis of SCH is primarily based on TSH levels. However, this can lead to overdiagnosis and overtreatment in elderly patients with SCH, as their TSH levels may naturally increase with age without indicating an underlying thyroid dysfunction (2).

Many studies have found that the incidence rate of SCH increases significantly with age (3, 4), which suggests that we need to consider the impact of aging on the hypothalamic-pituitary-thyroid (HPT) axis. For example, aging may weaken the circadian rhythm of TSH and reduce its responsiveness (5). According to the cross-sectional National Health and Nutrition Examination Survey (NHANES) III, the average TSH of adults aged 80 is 69% higher than that of adults aged 20 (6, 7). Data from Scottish, and Australia also confirm that TSH level increases with age (8–10). Our previous epidemiological survey in ten cities indicated that the prevalence of SCH in people over 65 years old was 19.87% according to the current TSH reference interval, but when the age-specific TSH reference range was used, the prevalence decreased to 3.3% (3). Although the mechanism is unclear, the increase in TSH in the elderly may be a normal phenomenon associated with aging. When the current diagnostic criteria are used, many elderly patients with no clinical significance will be diagnosed.

Prospective research on the natural outcome of the elderly indicated the above problem. In 2004, a study from Spain followed up 107 elderly patients with SCH over 55 years of age for 6 years (11), and the proportion of patients’ disease progression, maintenance, and recovery were 26.8%, 35.8%, and 37.4% respectively, that is, only a few patients had significant progress. In 2012, an American study conducted a 4-year follow-up of 459 elderly patients with SCH over 65 years old and found that 56% of the patients were in the state of SCH maintenance in the second and fourth years of follow-up (12). In addition, the remission rate of TPOAb-negative patients is significantly higher than that of TPOAb-positive patients. In 2017, a Chinese study conducted a 3-year follow-up of 505 patients with SCH over the age of 40 and found that only 3.4% had progressed, while 43.8% were in maintenance, and 49.7% returned to normal (13). It was also believed that TPOAb, TSH levels, creatinine, and total cholesterol levels were related to different outcomes of SCH. That is, many elderly patients with SCH may have stable or even recovery of their condition without any intervention, while only a few of them have progressed and need treatment, which suggests that using the current unified TSH reference interval of the entire population to diagnose SCH in the elderly may lead to overdiagnosis and overtreatment. To avoid this, it is recommended to establish age-specific TSH reference ranges for the elderly to better identify those who may require treatment. This approach can help prevent unnecessary interventions in patients with SCH and reduce potential adverse effects of overtreatment.

In recent years, there has been increasing attention from experts worldwide toward the management of SCH in elderly patients. Many countries have started to revise their guidelines accordingly to provide more tailored recommendations for the screening, diagnosis, and treatment of SCH in the elderly. In 2020, the French expert consensus proposed that individualized treatment should be adopted for elderly patients with SCH (14). In 2021, experts from China also advocated jointly determining whether treatment is needed according to age, TSH level, symptoms, cardiovascular risk factors, etc (15). The guidelines of other regions are listed in **Table 1**. These guidelines have great differences and lack reliable epidemiological research support, which is also one of the purposes of our prospective research.

**Table 1 T1:** Current guidance on the treatment of subclinical hypothyroidism in the elderly.

No.	Publication year	Organization	Main recommendations	
			TSH<10mIU/L	TSH≥10mIU/L
1 (16)	2012	American Thyroid Association (ATA)	Consider treatment if there are symptoms of hypothyroidism, TPOAb(+) or atherosclerosis, cardiovascular disease, heart failure, or risk factors of these diseases	Consider treatment
2 (17)	2013	European Thyroid Association (ETA)	Age<70 years: treat if there are symptoms; observe if there is no symptom	Age<70 years: treat
			Age>70 years: observe	Age>70 years: consider treatment if there are symptoms or cardiovascular risk factors
3 (18)	2013	The Thyroid Department of the Brazilian Society of Endocrinology and Metabolism	Age ≤ 65 years: observe if there are no comorbidities; consider to treat if it is possible to progress to hypothyroidism; if there is cardiovascular disease or its risk, consider to treat if TSH≥7 mIU/L; if there are hypothyroidism symptoms, the therapeutic test should be considered	Treat
			Age>65 years: observe	Treat
4 (19)	2018	National Institute for Health and Care Excellence (NICE)	Age <65 years: consider trial	Age <70 years: treat
			Age≥65 years: watch and wait	Age≥70 years: watch and wait
5 (20)	2020	Gulf Cooperation Council (GCC) Countries	TPOAb(+): treat	Treat
			TPOAb(-): treat if there are indications; otherwise, observe	
6 (15)	2021	Endocrine Metabolic Diseases Group of the Chinese Geriatrics Society, Thyroid Group of the Chinese Society of Endocrinology, Chinese Medical Association	60-70 years old: treat if TPOAb(+) or there are hypothyroidism symptoms or cardiovascular risk factors; otherwise, observe	60-70 years old: treat
			71-80 years old: observe	71-80 years old: treat if there are hypothyroidism symptoms or cardiovascular risk factors; otherwise, observe
			Age>80 years: obersve	Age>80 years: obersve

In the process of SCH, we need to consider the adverse outcomes of cardiovascular and cognitive functions. The thyroid hormone is closely related to the cardiovascular system and plays a key role in the regulation of cardiac muscle cell inotropic and chronotropic effects (21, 22). SCH is generally considered a risk factor for cardiovascular disease and cardiovascular-related death events. At present, some studies have shown that the prediction of cardiovascular disease and mortality in elderly patients with SCH should be based on age and TSH level (23–26). The prognosis of the elderly is good, and TSH>10mU/L is often associated with the occurrence of cardiovascular diseases, which need further confirmation. For cognitive function, the thyroid hormone plays a key role in brain development and maturation, so abnormal thyroid function and hormone secretion may affect the neuropsychiatric system (27). Although thyroid function examination is usually performed in patients with cognitive impairment or depression, the relationship between SCH and neurological and psychological functions is still unclear. However, previous research suggested that SCH in the elderly has nothing to do with cognitive decline or dementia events, so it may not be necessary to conduct SCH screening in the elderly with cognitive decline (28–30). It is noteworthy that some studies have found that elderly patients with SCH may be prone to depression, but the results are inconsistent (31–33). Therefore, our research will focus on the cardiovascular disease and depression of patients.

## Methods

### Research type

This study adopts the methodological strategy of the cohort study in analytical epidemiology to carry out various data collection, diagnostic test analysis around the gold standard and the test data of diagnostic subjects, and economic analysis.

### Research objectives and main results

The goal of this study is to prospectively follow up on elderly patients with SCH who are diagnosed using age-specific TSH reference intervals and non-age-specific TSH reference intervals, which aims to establish TSH reference intervals for different age groups to improve the diagnosis and management of SCH in the elderly. The main outcomes being assessed include thyroid function, hypothyroidism-related symptoms, cardiovascular events, cognition, depression, and fatigue, as well as economic and social benefits analysis. The above information will help make informed decisions about the best course of treatment for elderly patients with SCH.

### Study population

We are conducting a prospectively observational study on patients over 60 years of age diagnosed with SCH. The study was conducted in the First Affiliated Hospital of China Medical University and the West China Hospital of Sichuan University. Patients will be included from December 2022 to December 2023, and the follow-up data will be collected until December 2025.

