### Study follow-up assessments

When a patient has FT_4_ levels below the lower limit of the normal reference range during follow-up, follow-up is terminated and thyroid hormone replacement therapy will be initiated. For patients aged 60 to 70 years, start treatment when TSH≥10mIU/L. For patients aged 71 to 80 years, treatment begins when TSH≥10 mIU/L and is accompanied by symptoms of hypothyroidism. Normal value reference ranges will be established based on the TSH levels of 120 normal elderly individuals over 60. Elderly SCH patients screened according to the TSH reference interval in the normal population and the elderly population will be followed up every 6 months, including the subclinical hypothyroidism questionnaire, the Montreal Cognitive Assessment-Basic (MoCA-B), Hamilton Depression Scale (HAMD), Hypothyroidism Symptom Questionnaire (SRQ), frail scale(FRAIL), fatigue scale, EQ-5D, thyroid function, blood lipid analysis, carotid color ultrasound, and thyroid ultrasound. The estimated sample size is 438. Patients diagnosed with different TSH reference intervals will be compared for cognitive function, depression scores, hypothyroidism, fatigue severity, carotid atherosclerosis, lipid profile, and cardiocerebrovascular complications. Besides, TSH reference intervals will be applied to calculate medical costs and evaluate the economic benefits of multiple follow-ups of patients with SCH. The research design can be seen in **Figure 1**.

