### Data analysis

We will calculate age-specific TSH reference intervals based on the obtained data, analyze the natural outcomes, the occurrence of cardiovascular events, cognitive status, depression, and fatigue of elderly patients with SCH diagnosed under different reference intervals, and conduct economic analysis.

Continuous data will be expressed as mean ± standard deviation or median with a range of quartiles. Classification data will be expressed in numbers with percentages. Cox proportional risk model will be used to evaluate survival results. The variables measured several times during the follow-up period will be compared with the paired t-test according to the clinical management used. The significance level will be set to 0.05, and R software, prodlim, and Cairo software will be used to analyze the data.

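### By the progression rates the article quotes, 438 patients followed for 2-3 years give about 12 to 53 endpoint events: too few at the low end for an informative Cox comparison, and below 80% power for a hazard ratio of 2 at either rate

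*Protocol article*

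**What the plan says.** The Study population section fixes the calendar: "Patients will be included from December 2022 to December 2023, and the follow-up data will be collected until December 2025". The section on follow-up assessments gives the size, "The estimated sample size is 438", and sets visits with thyroid function tests every six months.

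The Abstract (Methods) makes the endpoint depend on age. For patients aged 60-80, "TSH levels greater than or equal to 10mIU/L or a decline in FT_4_ will be used as the endpoint event"; above 80, only a fall in FT4 counts. The Data analysis section says "Cox proportional risk model will be used to evaluate survival results", sets significance at 0.05, and assigns variables measured repeatedly to paired t-tests. It does not name the exposure for the Cox model.

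On how often SCH progresses, the Introduction cites a Chinese cohort (n = 505, older than 40, observed for three years) with this result: "found that only 3.4% had progressed, while 43.8% were in maintenance, and 49.7% returned to normal". It also quotes a Spanish study that "followed up 107 elderly patients with SCH over 55 years of age for 6 years", with 26.8% progressing. It concludes that only a minority progress. A third, American cohort is cited without a progression rate.

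**The concern.** The study argues that most elderly patients with SCH do not progress, and it wants to identify those who do. The rarer progression is, the better the argument for over-diagnosis, but the fewer events there are for a Cox model.

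Over-diagnosis is largely a question of absolute risk: how many of the patients labelled by the general limit go on to the endpoint. A hazard ratio from few events does not answer that. It would also usually be non-significant whether or not prognosis differs, and in a study meant to support age-specific limits such a result could be taken as support for them.

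**Working it through.** **Inputs from the article.** N = 438. Accrual of 12 months closing in December 2023 and data to December 2025 give 2 to 3 years per patient. Rate A is 3.4% in 3 years (age over 40, n = 505). Rate B is 26.8% in 6 years (age over 55, n = 107). Alpha is 0.05.

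**Assumptions.** Constant hazard, uniform accrual, no dropout, two-sided test, and progression in the cited studies comparable with this endpoint. The article gives no basis for 438 and no expected event count, so there is no planned figure to reproduce.

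**Step 1: hazard**, h = -ln(1 - p)/T.
- A: -ln(0.966)/3 = 0.0115 per year
- B: -ln(0.732)/6 = 0.0520 per year

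**Step 2: expected events** = 438 × the mean of 1 - exp(-h·t) for t uniform on 2 to 3 years.

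| Rate | All followed 2 y | Uniform 2-3 y | All followed 3 y | Uniform, 20% loss |
|---|---|---|---|---|
| A | 10.0 | 12.4 | 14.9 | 9.9 |
| B | 43.3 | 53.3 | 63.3 | 42.6 |

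**Step 3: precision and power** for a two-group comparison, SE(log HR) = 1/√(d·q·(1-q)), with d events and a fraction q in the smaller group. The article does not state q, so two values are shown. One is 50:50. The other is 16.6%, the ratio of the SCH prevalences quoted in the Introduction for people over 65 (3.3/19.87 = 0.166).

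| Events | q | SE | 95% CI factor either way | Power, HR 2 | Power, HR 3 | HR detectable with 80% power |
|---|---|---|---|---|---|---|
| 12.4 | 0.50 | 0.57 | 3.0 | 23% | 49% | 4.9 |
| 12.4 | 0.166 | 0.76 | 4.5 | 15% | 30% | 8.5 |
| 53.3 | 0.50 | 0.27 | 1.7 | 72% | 98% | 2.2 |
| 53.3 | 0.166 | 0.37 | 2.1 | 47% | 85% | 2.8 |

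Example for row 2: 1/√(12.4 × 0.166 × 0.834) = 0.76, and exp(1.96 × 0.76) ≈ 4.5.

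**Step 4: events needed for 80% power at HR 2**, (1.96 + 0.84)²/[(ln 2)²·q(1-q)]: about 66 at 50:50 and about 118 at 16.6%. Even rate B with every patient followed for 3 years (63 events) stays below 66.

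**Step 5: absolute risk.** As a crude illustration, 12 of 438 is 2.7% with an exact 95% CI of 1.4% to 4.7%. The same dozen events that leave a hazard ratio uncertain by a factor of 3 or more still bound the overall risk fairly closely.

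**The case against.** **The low count is only one scenario.** This stands. A reader might infer that the event will occur in about a dozen patients and that the Cox model cannot show who progresses. The documents do not support that. The second quoted rate gives about 53 events, with 85% to 98% power for a hazard ratio of 3, and comes from patients aged over 55, nearer to this study's entry age of 60 than the over-40 cohort. The low scenario still deserves weight: that cohort is Chinese, its follow-up is close to this study's, and the endpoint above 80 is narrower.

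**Neither rate maps exactly to this endpoint.** This stands too. The article does not define progression in the cited studies. If the 3.4% meant overt hypothyroidism only, the composite used here would be more frequent.

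**The contrast is assumed.** Correct. No exposure is named for the Cox model, and the 16.6% split is a prevalence ratio, not a recruitment plan. Inclusion criterion 3, read literally, admits only patients between the old and new limits and so leaves no group above the new one. The 50:50 figures show that the shortfall at HR 2 does not depend on the unequal split.

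**The threshold event is not the whole prognosis question.** Correct. The objectives already list thyroid function, symptoms, cardiovascular events, cognition, depression and fatigue among the main outcomes, and the Abstract plans to describe change in FT4. It would be wrong to say that the plan rests on the threshold event alone.

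**No rule reads a null result as safety.** Also correct. The article states no such rule. The risk is that a null result could be read that way.

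**Power details may sit in a full protocol or SAP not shown.** They may, so their absence is not the point here. The point is that the named methods fit poorly with the event numbers implied by the article's own figures.

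**Conclusion.** The point holds as a matter of precision. The quoted rates imply about 12 to 53 events (10 to 63 across the 2- and 3-year extremes without dropout). At the low end a Cox comparison is uninformative, with a detectable hazard ratio of about 5 at 50:50 and about 8 at 16.6%. At the high end it is usable for a hazard ratio of 3. At neither rate does it reach 80% power for a hazard ratio of 2: 23% and 72% at 50:50, 15% and 47% at 16.6%. These figures rest on the assumptions listed above, of which comparability of the cited progression with this endpoint is the weakest. The change is worth making because it is cheap and gives an interpretable answer at either rate.

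**What to change.** Amend the Data analysis section, keeping the sample, the calendar and the endpoint as they are.

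1. Report the endpoint event as absolute cumulative incidence at 2 and 3 years with 95% confidence intervals, overall and by baseline TSH position, using a method that allows for the variable 2-3-year follow-up. Base statements about over-diagnosis on the upper confidence bound, not on a non-significant hazard ratio. The investigators should state beforehand what upper bound they would regard as low.
2. Limit any Cox model to one or two terms if events are near the low end.
3. Alongside the event, and not in place of it, analyse all six-monthly FT4 and TSH values with a longitudinal mixed model instead of paired t-tests. The model must allow for truncation when treatment starts, since that is linked to the same measurements, and for regression to the mean in TSH, since patients enter on a raised value.

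The cost is some extra analysis work and a less striking headline than a single hazard ratio. No additional patients or visits are needed.

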### Inclusion criteria and exclusion criteria

Inclusion criteria:

Elderly patients with SCH will be included according to the elderly and the general population-specific reference ranges, respectively.

(1) Inpatients and/or outpatients aged≥60 years.(2) The levels of free triiodothyronine(FT_3_) and FT_4_ are within the normal range.(3) TSH is greater than the upper limit of the normal reference range (old standard) and less than the upper limit of the normal reference range (new standard).

Exclusion criteria:

(1) Does not meet the inclusion criteria, does not sign the consent form, or participates involuntarily.(2) Exit halfway due to various reasons.(3) Unable to cooperate with the project team to complete all inspection contents.(4) Other factors leading to TSH increase. 1) increased TSH caused by measurement errors; 2) convalescence stage of the euthyroid sick syndrome; 3) central hypothyroidism; 4) renal insufficiency; 5) lack of glucocorticoids; 6) the recovery stage of thyroid function in subacute thyroiditis; 7) having taken amiodarone or lithium; 8) other interfering factors.

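### Inpatients are eligible and no stated rule covers care setting or timing of the baseline scales, so recovery from the admitting illness can be read as improvement in scale scores under untreated SCH

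*Protocol article*

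**What the plan says.** The first inclusion criterion (Inclusion criteria and exclusion criteria) is "Inpatients and/or outpatients aged≥60 years". The abstract's Methods paragraph says that after consent "their initial diagnosis information will be registered, and they will be asked to fill out questionnaires", and names MoCA-B, HAMD, the hypothyroid symptom questionnaire, FRAIL, a fatigue scale and EQ-5D. Under Study follow-up assessments, patients "will be followed up every 6 months" with the same instruments.

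On analysis, the Data analysis section states: "The variables measured several times during the follow-up period will be compared with the paired t-test according to the clinical management used". Study follow-up assessments adds a comparison between groups: "Patients diagnosed with different TSH reference intervals will be compared for cognitive function, depression scores, hypothyroidism, fatigue severity".

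Two exclusions bear on illness. One is "convalescence stage of the euthyroid sick syndrome", listed among the other causes of a raised TSH. The second is "Unable to cooperate with the project team to complete all inspection contents". Care setting does not appear again after the inclusion criterion, either as a stratum or as a covariate.

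**The concern.** A patient enrolled in hospital may score worse on mood, fatigue, frailty, symptoms, cognition and quality of life because of the illness that led to admission. Six months later those scores may be better whatever the thyroid has done. A paired test has no comparator that could subtract this recovery: the 120 normal individuals serve to set reference ranges, and no follow-up of them is described.

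The direction matters. The Introduction and Discussion argue that many elderly patients with SCH stay stable or recover without treatment. Recovery from an admission moves the scales the same way, and could mask a real decline in some patients. Symptoms, cognition, depression and fatigue are named among the main outcomes under Research objectives and main results, so these are not minor measures.

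**Working it through.** **What the stated safeguards cover**

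- The euthyroid-sick exclusion concerns why TSH is raised. It partly protects the thyroid results and does nothing for the scales.
- The exclusion for inability to complete the assessments may remove the sickest inpatients. It does not remove a cooperative inpatient who scores badly because of the current illness.
- The repeat measurement described under Limitations concerns TSH only.

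**Inputs**

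- From the article: n = 438 and a significance level of 0.05, taken here as two-sided. The article does not give the inputs behind 438, so it cannot be reproduced; it is used as given, and the point does not depend on it.
- Assumed: inpatient share f of 10%, 30% or 50%; mean recovery d in inpatients of 0.2 or 0.5 SD of the scale; no change in outpatients and no true SCH-related change; correlation ρ between visits of 0.5 or 0.7.

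**Formulas** (normal approximation to the paired t-test)

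- Spurious mean change = f × d.
- SD of change = √(2(1 − ρ)), which is 1.00 at ρ = 0.5 and √0.6 = 0.775 at ρ = 0.7.
- Expected test statistic λ = f × d × √438 / SD of change, with √438 = 20.93.
- Rejection rate = Φ(λ − 1.96) + Φ(−λ − 1.96).

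Example: f = 30%, d = 0.5, ρ = 0.5 gives 0.30 × 0.5 = 0.15 SD, λ = 0.15 × 20.93 = 3.14, and a rejection rate of Φ(1.18) = 88%.

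| Inpatient share | Recovery (SD) | Spurious mean change (SD) | False rejection, ρ = 0.5 | False rejection, ρ = 0.7 |
|---|---|---|---|---|
| 10% | 0.2 | 0.02 | 7% | 8% |
| 10% | 0.5 | 0.05 | 18% | 27% |
| 30% | 0.2 | 0.06 | 24% | 37% |
| 30% | 0.5 | 0.15 | 88% | 98% |
| 50% | 0.2 | 0.10 | 55% | 77% |
| 50% | 0.5 | 0.25 | over 99% | over 99% |

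At ρ = 0.5 the expected statistic reaches 1.96 when f = 1.96 / (20.93 × d). That is 19% inpatients if d = 0.5, but 47% if d = 0.2. No single threshold share can be quoted without fixing the recovery.

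The rejection rates assume one test on all 438 patients. Attrition, or separate tests by clinical management, would lower them. The mean shift of f × d within any tested set does not depend on n.

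**Between reference-interval groups**

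Bias in the difference in change = (difference in inpatient share) × d. It is zero if the shares are equal. A 10-point difference gives 0.1 × 0.2 = 0.02 to 0.1 × 0.5 = 0.05 SD, and a 20-point difference gives 0.04 to 0.10 SD.

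**The case against.** The strongest case against has four parts.

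1. **Timing is inferred.** The article says neither that admissions are acute nor that inpatients are scored in hospital; some stays may be elective. This stands, so the point is conditional. Even so, the scales are tied to registration of the diagnosis, and nothing stated delays them for an inpatient.

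2. **The paired test may not be a pooled before-and-after test.** The text refers to variables measured repeatedly over follow-up and to clinical management; it names no contrast between baseline and six months. This stands too. If the enrolment assessment is left out of the test, the problem goes away for that test, but the text does not say that it is left out.

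3. **An article may leave visit procedures, covariates and sensitivity analyses to the full protocol or analysis plan.** That is fair, and silence on those details alone would be no finding. The point rests on what is stated in combination: both settings eligible, scales at registration, and a within-patient test that cannot separate the two sources of change.

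4. **The size is almost wholly assumed.** Only 438 and 0.05 come from the article. This is correct and limits the verdict to a range.

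A reader might also infer that the natural-course result as a whole is biased. The article does not support that. Its endpoint event is biochemical, based on FT4 and, at ages 60 to 80, also on TSH. The Data analysis section lists natural outcomes apart from the scales: "analyze the natural outcomes, the occurrence of cardiovascular events, cognitive status, depression, and fatigue of elderly patients with SCH". A better fatigue or depression score does not change a TSH/FT4 event. Nor does anything suggest that inpatient share differs between the reference-interval groups, so bias in that comparison is a possibility only.

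**Conclusion.** The point holds for within-patient change in the scales. If a material share of patients is enrolled and scored during or near a hospital stay, the stated rules can produce a spurious improvement that would be credited to the course of untreated SCH. Under the assumed shares and recoveries this is 0.02 to 0.25 SD. At the low end it is negligible, with a false-positive rate of 7% to 8% against a nominal 5%; at the high end it would dominate the result. The article gives no inpatient share and so no means of placing the study within that range. It would be too strong to say that the improvement will occur, that inpatients are known to be scored while acutely ill, or that the TSH/FT4 progression result is affected.

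**What to change.** - Record care setting at enrolment. For patients already enrolled it should be recoverable from hospital records.
- Analyse change in the scales stratified by care setting, or adjusted for it, and report the inpatient share by reference-interval group and by hospital.
- Report outpatients alone as a sensitivity analysis.
- For inpatients still to be enrolled, take the baseline scales once the admitting illness has settled. If recruitment has closed as planned in December 2023, only the analysis steps apply.
- Do not use the six-month visit as baseline in the main analysis. Follow-up ends when FT4 falls below range, so inpatients who reach that point before six months would have no change data, and the early progressors would be lost.

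The cost is small: somewhat lower precision in the outpatient-only analysis and a slightly later baseline for some inpatients. The analysis steps need no extra visit or staff.
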